## Abstract

**Background:**

Growing evidence exists that living with an ICD can lead to fear and avoidance behaviour including the avoidance of physical activity. It has been suggested that psychological stress can increase the risk of shock and predict death. Small studies have indicated a beneficial effect arising from exercise training and psychological intervention, therefore a large-scale rehabilitation programme was set up.

**Methods/Design:**

A mixed methods embedded experimental design was chosen to include both quantitative and qualitative measures. A randomised clinical trial is its primary component. 196 patients (power-calculated) were block randomised to either a control group or intervention group at a single centre. The intervention consists of a 1-year psycho-educational component provided by two nurses and a 12-week exercise training component provided by two physiotherapists. Our hypothesis is that the COPE-ICD programme will reduce avoidance behaviour, sexual dysfunction and increase quality of life, increase physical capability, reduce the number of treatment-demanding arrhythmias, reduce mortality and acute re-hospitalisation, reduce sickness leading to absence from work and be cost-effective. A blinded investigator will perform all physical tests and data collection.

**Discussion:**

Most participants are men (79%) with a mean age of 58 (range 20-85). Most ICD implantations are on primary prophylactic indication (66%). 44% is NYHA II. Mean walk capacity (6MWT) is 417 m. Mean perception of General Health (SF-36) is PCS 42.6 and MCS 47.1.

A large-scale ICD rehabilitation trial including psycho-educational intervention and exercise training has been initiated and will report findings starting in 2011.

**Trial Registration:**

ClinicalTrials.gov: NCT00569478

## Background

Treatment with Implanted Cardioverter Defibrillators (ICD) has reduced mortality remarkably during the past 20 years. It has resulted in new, more extensive guidelines for the implantation of ICDs [1]. The average ICD implantation rate in Europe is 140 per million inhabitants (in Denmark 180 per million) and in the USA the rate is considerably higher, 416 per million [2]. Studies have shown that living with an ICD can lead to anxiety, fear of shock and avoidance of situations, places and objects that the patients associate with shock. It often leads to social isolation, avoidance of physical activity, including sexual activity and mood disturbances [3-8]. In addition, it has been suggested that negative emotions could be the cause rather than the result of arrhythmia, and that psychological stress can increase the risk of shock [9-11]. Furthermore, psychosocial status seems to predict mortality [12]. It is unclear if cardiac rehabilitation can reduce the risk of shock or death.

During the past 10 years several, often small, interventional studies have been carried out aiming to improve every day functioning of patients with ICD.

### Exercise training

Patients enrolled in out-patient rehabilitation (OCR) tend to exercise more often, 4 times a week versus - 3 times a week in the case of non-OCR patients, and with a higher intensity 5.3 METS (metabolic equivalent) versus 3.5 METS in non-OCR patients [13]. Exercise training in a rehabilitation format has been shown to be safe [14-17], to improve cardiopulmonary fitness e.g. exercise time [14], METS [18], Peak Vo2 [14-17] and reduce anxiety [14] and improve quality of life [15].

### Psycho-intervention

Psychological [19]/psycho educational [20-22]/cognitive behavioural [11,23,24] interventions have either a group format [24] or an individual format [19,20] with face to face consultations [24] or telephone counselling [11,19,24]. Psychological intervention seems to have a beneficial effect on anxiety and perceived physical health in patients younger than 65 years but may lead to symptom increase in older patients [19]. Psycho-educational intervention seems to reduce anxiety [20,21,25] and enhance knowledge [20]. However in the computer based format there were no beneficial effects [22]. Cognitive behavioural rehabilitation has shown to improve physical health, reduce anxiety [11,23] and depression, and lower unplanned admissions [23]. However in a group format no difference in quality of life was found [24].

### Combined interventions

A few randomized trials have combined exercise training and cognitive behavioural intervention. In a study by Frizelle et al. from 2004, 22 patients were included, half in an intervention group and half in a waiting group, beginning rehabilitation after 3 months. The intervention consisted of a weekly two-hour group meeting over a 6 week period and a follow up telephone call at 9 weeks. Significant improvements in anxiety, depression, quality of life and physical capacity were observed [26]. Similarly Fitchet et al. compared 16 patients randomised either to a 12 week (twice weekly) rehabilitation programme or a waiting group, beginning rehabilitation after 3 months. The intervention consisted of exercise training and psycho-educational intervention in a group format. This resulted in improved exercise time, and reduced anxiety and depression [27].There have been calls for a well-powered study combining psycho-educational intervention and exercise training [21]. We have now developed and completed enrolment for just such a study. The purpose of the COPE-ICD trial, to our knowledge, the largest randomised clinical intervention trial studying ICD rehabilitation, is to describe the effect and meaning of an outpatient programme including psycho-educational consultations and exercise training for patients with ICD. This paper summarises the study design and the baseline characteristics of the participants.

### Hypothesis

Our hypothesis is that the COPE-ICD programme will:

• reduce avoidance behaviour and increase quality of life

• reduce fear of exercise and increase physical capability.

• reduce sexual dysfunction

• reduce the number of treatment-demanding arrhythmias and ICD shocks.

• reduce mortality

• reduce acute re-hospitalization

• reduce sickness absence and improve employment status in the long term

• be cost effective

## Methods/Design

### Trial design

The COPE-ICD trial combines quantitative and qualitative research methods. The methods are integrated by applying a mixed methods embedded experimental design (Figure 1) [28]. The quantitative method utilises the traditional randomised controlled trial (RCT). The qualitative methods utilises extensive interviews of a small selected subset of intervention patients. The qualitative data will help explain the quantitative findings. The rationale for this approach is that the quantitative data and their subsequent analysis provide a general understanding of the research problem. The qualitative data and their analysis refine and explain the statistical results by exploring participants' views in more depth.

**Figure 1 F1:**
[figure not shown]
**Trial Design**.

### Participants

The setting is a large university hospital with a volume of approximately 300 first time ICD implantations every year.

#### Eligibility

##### Inclusion

- Patients who received an ICD for the first time, and who prior to hospital discharge agreed to participate in the entire programme.

- Patients with physician permission prior to randomization to participate in the physical training programme.

##### Exclusion

- Patients who do not understand the study instructions.

- Patients who are under 18 years of age.

- Patients who are diagnosed with a psychiatric disease.

- Patients with other somatic diseases, where recovery might influence the study.

### Randomisation

Before randomisation baseline data were collected. Patients were randomised while in hospital.

The enrolling research assistant or primary investigator called for randomization allocation. Randomisation (block of 4) was done by voice-respondent in a 1:1 ratio to intervention group or control group (standard care) and there was stratification according to gender and left ventricular ejection fraction (below or above 35%).

### Intervention COPE-ICD

#### Psycho-educational intervention

The programme is based on a humanistic approach, focusing on psychosocial support and education. The programme is directed towards the parameters that ICDs reportedly affect. The content is made up of information and education focused on managing life with an ICD, including emotional reactions (Table 1) using a holistic view on the person and establishment of a joint approach to disease management and coping. Nursing care is inspired by R.R Parse's Human Becoming Practice Methodologies 3 dimensions [29] that are interpreted as: 1, discuss and give meaning to the past, present and future 2, explore and discuss events and possibilities and 3, move along with envisioned possibilities. According to this theory there are 3 ways of changing health: creative imaging that is see, hear and feel what a situation might be like if lived in a different way, affirming personal patterns and value priorities, and shedding light on paradoxes, that is looking at the incongruence in a situation and changing the view held of something. The nurse is true present in the process through discussions, silent immersion and reflection. The consultations take place in a quiet setting at the out-patient clinic. The nurse is able to facilitate contact to or seek advice with a physician or a technician.

**Table 1 T1:** Inspiration Guide for Nursing Consultations

	1	2	3	4	5	6	7	8	9
What happened since you were here last time? How have you been?	x	x	x	x	x	x	x	x	x

Discuss the events leading up to the ICD implant. Experiences before and during admission.	x								

Address present thoughts and questions	x	x	x	x	x	x	x	x	x

Were there any episodes from the ICD?	x	x	x	x	x	x	x	x	x

How did you having an ICD affect your life? Are there any activities you avoid? Are there any places you avoid? Are there objects you avoid?		x							

Did you make an appointment with the physiotherapist/how is training going?			x	x	x	x	x	x	x

Discuss family, how do they tackle, changing patters in the family?				x	x	x			

Information, technical/recommendations.	x				x				

Shock (ad hoc)/phantom shock			x						

Changing view on the body?				x					

Driving		x							

Sexuality, is this affected?				x				x	

The patients consult the nurse in person or by phone once a month for 6 months, and every 2 months thereafter, for the following 6 months. The frequency is based on clinical experience where transportation to the hospital and the need for psycho-educational support are considered. Relatives are invited to participate once or twice if needed. The psycho-educational part of the intervention is performed by two nurses with 10 years of clinical experience each in the care for patients with ICDs. The nurses do not care for ICD patients at the in-hospital unit during the project period to prevent "contamination" of the control group.

#### Exercise training program

Three months after the ICD implantation, training is done twice a week for twelve weeks. The three month delay was chosen to secure stability [20]. The physical training program consists of an individual consultation with the physiotherapist and an individually tailored training programme. A test of aerobic functioning, patients' experiences and usual activities are elements in planning an individual programme. Patients do both resistance and aerobic training, to gain muscle strength and endurance and to gain reduction in after load with a decrease in systemic resistance [30]. The training has either a supervised group format in-hospital or is done at home or in a local hospital rehabilitation setting. The patients use pulse watches while exercising, to ensure that the recommended intensity of the training programme is obtained, and to ensure that the ICD activation threshold is not reached. During the physical training the pulse is noted, at 4 specific times. The patients exercise aerobically, at 50-80% of their estimated maximum pulse, calculated by the Karvonen formula [31]. The target exercise heart rate is close to 80% of their maximum capacity. Patients are encouraged to exercise intensively, to obtain the maximum effect of the training, but not to fatigue themselves. Resistance training is done by 60-80% of one-repetition maximum (1-RM). The training pulse is allowed to rise to a maximum 10 - 15 beats below the ICD activation threshold [30]. To obtain cardiovascular adjustment, it is important to warm up and cool down, to minimize the risk of ischemia and arrhythmia [27,32]. The patients primarily exercise in an upright position, to reduce left ventricular filling pressure and minimize the risk of ischemia or heart failure ventricular arrhythmia [32].

##### Group training at the hospital

The exercise training takes place in a supervised group with planned elements that are individually adjusted with respect to capacity, and risk of injuries.

One session consists of the following; 10 min. warm up, 8 min. biking, 8 min. walking/jogging/running, 8 min. individual aerobic endurance training e.g. step, stairway or running and resistance training of the major muscle groups. The session ends with 10 min. cool down and relaxation. Two physiotherapists with 2-3 years of experience each ran the exercise training programme.

##### Home training

Patients that cannot not attend exercise training at the hospital, are given an individual programme based on the above principles and instructed how to use a pulse watch with extended memory to monitor all training sessions. This is done in order to guide patients and to ensure adherence to instructions.

An overview of the intervention timeline and data collection is presented in Figure 2.

**Figure 2 F2:**
[figure not shown]
**Timeline**.

#### Standard care

Patients in the control group follow the standard care procedure, which is medical follow-up and an invitation to participate in a 2 hour group meeting, which includes information about the ICD and exchange of experiences among patients. In the standard care group no psycho-educational follow-up or exercise training are provided. A bias may occur if patients are offered cardiac rehabilitation at their local hospital. As a national law encourages rehabilitation for all cardiac patients, it is not possible to completely avoid participation in local initiatives. Patients are asked whether they had participated in such activities at the12 months follow-up.

### Outcomes

Using questionnaires, interviews, exercise-tests, a 6-minute walk test (6-MWT), interrogation of the ICD and register-based follow-up, the effect and meaning of the programme are evaluated (Table 2). The pre-training exercise test is performed at 3 months and therefore not reported here.

**Table 2 T2:** Outcome Measures

Measurement	Time
**SF-36**	Baseline, 3-6-12 month

QLI-C	Baseline, 3-6-12 month

IDAS	Baseline, 3-6-12 month

Sex after ICD survey	6 month

ICD and Avoidance Survey	6-12 month

SCA knowledge assessment	Baseline, 12 month

**Exercise test**, 6MWT	3-6 month

ICD interrogation	3-6-12 month

Work	12 month

Rehabilitation elsewhere	12 month

Qualitative interview	12 month

Registry data	2 years

SF-36 and exercise test are primary outcome measures.

Primary outcome measures: Due to the nature of rehabilitation, including both physical and psychological components, the two primary outcome measures are perceived health measured by the Short Form-36 [33,34] questionnaire and Peak VO2, measured by a standardized protocol according to guidelines [35]. The test is performed on bicycle ergometer with an initial workload of 12.5 W and increased 12.5 w every minute until exhaustion or at 5 beats/min heart rate below ICD activation threshold. No gas analyses are conducted.

Secondary outcome measures: Physical capability is measured by an exercise test combined with the six minutes walk tests which have been proved to be effective measures of functional capacity in patients performing cardiac rehabilitation [30,36,37]. Further, exercise training data consist of the number of sessions, duration and heart rate.

Ventricular arrhythmia: 1. ICD-shock 2. Anti-tachycardia pacing is registered by interrogation of the ICD.

Questionnaires: Quality of life is measured by Quality of Life Index-Cardiac version (QLI-C) [38], knowledge of the ICD by Sudden Cardiac Death (SCD) knowledge assessment [20], ICD-adaptation using Implanted Devices Adjustment Scale (IDAS) [39], sexual problems or dysfunction by the Sex After ICD Survey [40] and avoidance behaviour is measured by ICD and Avoidance Survey [40].

Ancillary questions developed for this study: amount of participation in rehabilitation outside the project, and work status/sick leave before and after ICD implantation.

Registry data: Registry data is collected regarding death, hospitalisation, emergency room visits, outpatient visits, medication and employment status. The national registries function very well with a small percentage of lost data and thus are well suited to measure effects, even in small patient populations. Data is extracted from the Danish National Patient Register, the Danish National Health Service Register, the Danish National Prescription Registry and the Danish National Causes of Death Register.

Demographic variables and diagnoses are collected from medical records.

The qualitative study:

The qualitative study seeks to answer the following questions in order to fulfil the purpose of the trial:

Thematic research questions:

- What are the experiences of participating in the COPE-ICD program?

- What is the meaning of participating in the program?

- Which components of the outpatient program are meaningful, and how are they meaningful?

Ten patients (10%) from the intervention group are interviewed at the end of intervention. Qualified interviewees are chosen (knowledgeable, articulate), representative in terms of stratification, gender and left ventricular ejection fraction (LVEF) and according to the reason for ICD implantation (primary/secondary prevention) to achieve maximum variation [41]. The analysis is inspired by Ricoeur's theory of interpretation and consists of three levels: naive reading, structured analysis and critical interpretation and discussion [42].

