### Statistical methods

The statistical analyses of the effects of rehabilitation are conducted based on a predefined statistical protocol using SPSS 17.0 for Windows. The analysis will adopt an analytical approach on all available data, meaning that all data obtained are included in analyses, regardless of adherence to the study protocol. Only data from patients following through the program will be included in the analysis of the endpoints. Accordingly, there is no imputation of missing data. Questionnaire responses will be converted to numerical scores using standard methodologies. Continuous data are checked for normality of distribution, and log-transformed if required. The baseline characteristics will be presented by group to present similarities across treatment, but according to recommendations no significant testing will be performed [43]. The socio-demographic and clinical characteristics of individuals who drop out from the study will be compared with those who completed the study and drop-out characteristics between groups will be compared. The effectiveness of the intervention will be examined using blinded analysis of variance. The primary comparisons will be Two independent samples T-test for the mean difference between two independent samples. Paired T-tests of equality of means will be used for within group analysis of difference over time. Further, univariable and multivariable regression analysis will also be used to investigate the effect of the intervention on the endpoints. The type of regression analysis will depend on the endpoint in question. Demographic, clinical and questionnaire data will be included in multivariable analysis in order to control for their potential confounding effects. The level of significance is set at p < 0.05. Data will, for continues data, be shown as means ± standard deviation or percentage. Categorical data will be shown as percent. Twelve month follow-up data and results obtained from Danish registries regarding hospitalisations are used for follow-up comparison. Due to the skewed distribution of length of hospital stay and repeated measurements of hospital admissions on patients these register-based tertiary outcomes will be analyzed using multivariate random-effect modelling with patients as random effects. Further analysis will be conducted using the Cox regression model including time to first event as outcome variable. At baseline 46% (n = 91) of the population was employed. This is a rather small number of patients and sickness absence will be included as a measure when evaluating employment status. The direct costs of healthcare are calculated by a retrospective top-down method [44]. All other costs are extracted from relevant registers.

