### Baseline measures

Most participants are men (79%) and the mean age was 58 (SD 13.2), range 20-85. The mean LVEF is 32 (SD17.5) and most (46%) are NYHA class 2 and 64% received the ICD for primary prevention (Table 3). The medication status at baseline is presented in Table 4. The mean walk capacity measured by 6MWT is 417 m., Table 5. The perception of health measured by SF-36 is 42.6 for physical component scale (PCS) and 47.1 for mental component scale (MCS), a higher score indicating better perception of health, scale range 0-100 (Table 6). Quality of life score is 26.4 (Table 6), scale range from 0-36, a higher score indicating better quality of life. Baseline knowledge of the ICD score is 20 (Table 6), scale range 0-25.

**Table 3 T3:** Demographic and Physical Profile

	Control gr. n (%)	Intervention gr. n (%)
Male gender	76 (78)	79 (80)

Age (mean)	58	58

Employed	50 (52)	41 (42)

Primary prophylactic indication	67 (69)	63 (64)

VF prior to ICD implantation	20 (20)	21 (21)

LVEF (mean/SD) 73% of tot pop ≤ 35	32.7 (18)	32.2 (17)

NYHA I	18 (19)	30 (31)

NYHA II	44 (46)	42 (43)

NYHA III	32 (33)	24 (25)

NYHA IV	1(1)	2 (2)

BMI ≥ 30	19 (20)	24 (24)

Atial fibrillation	21 (22)	27 (27)

CRT device	9 (9)	14 (14)

History of IHD	57 (59)	45 (46)

Previous MI	33 (34)	20 (21)

Previous PCI	29 (30)	28 (29)

Previous CABG	21 (22)	14 (15)

History of HF	73 (75)	76 (78)

Diabetes	10 (10)	12 (12)

Hypertension	23 (24)	18 (18)

COLD	1 (1)	2 (2)

Other chronic disease	24 (25)	27 (28)

CRT: Coronary resync. therapy. IHD: Ischemic heart disease. MI: Myocardial infarction. PCI: Percutaniuos catheter intervention. CABG: Coronary artery bypass graft. HF: Heart failure. COLD: Chronic Obstructive Lung Disease.

**Table 4 T4:** Baseline Medication

	Control gr. n (%)	Intervention gr. n (%)
Betablockers	83 (86)	76 (76)

Calcium antagonist	6 (6)	18 (18)

Amiodarone	8 (8)	11 (11)

ACE inhibitors	67 (69)	69 (69)

Digoxin	8 (8)	12 (12)

Prolonged nitrates	7 (7)	4 (4)

Insulin	4 (4)	5 (5)

**Table 5 T5:** 6 MWT Baseline

	**Control gr. score**.	**Intervention gr. score**.
Distance meter (SD)	415 (118)	420 (112)

*Shortness of breath Pre-test (CI)	1.1 (0.7-1.3)	0.9 (0.5-1.3)

*Shortness of breath Post-test (CI)	3.2 (2.6-3.8)	2.8 (2.2-3.4)

*Exertion pre-test (CI)	2.1 (1.5-2.7)	1.7 (1.3-2.3)

*Exertion post-test (CI)	2.5 (1.8-3.1)	2.2 (1.5-2.8)

*BORG CR 10 Scale.

Mean values and 95% confidence interval

**Table 6 T6:** SF-36, QoL -cardiac version, SCA knowledge.

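### The exercise co-primary has no pre-randomisation value; it should be the 6-month between-arm comparison adjusted for baseline 6MWT, with the 3-month test as neither baseline nor covariate

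*Protocol article*

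**What the plan says.** All references are to the Protocol article.

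- **Order of events (Randomisation).** "Before randomisation baseline data were collected. Patients were randomised while in hospital". Allocation is 1:1, stratified by gender and LVEF around 35%.
- **Timing of the exercise test (Outcomes, Table 2).** The row reads "Exercise test, 6MWT 3-6 month". The text adds: "The pre-training exercise test is performed at 3 months and therefore not reported here". SF-36, the other co-primary, has a baseline measurement.
- **Intervention before 3 months (Psycho-educational intervention).** "The patients consult the nurse in person or by phone once a month for 6 months". Table 1 raises avoided activities at the second consultation and the physiotherapy appointment or training from the third. The Exercise training program section starts training three months after implantation.
- **Baseline 6MWT (Baseline measures).** "The mean walk capacity measured by 6MWT is 417 m., Table 5". Table 5 gives 415 m (SD 118) in the control group and 420 m (SD 112) in the intervention group.
- **Analysis (Statistical methods).** The primary comparison is a two-independent-samples t-test, with no statement of whether it is applied to the 6-month value or to change. "Paired T-tests of equality of means will be used for within group analysis of difference over time". Regression models with demographic, clinical and questionnaire covariates are listed as further analyses.

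**The concern.** The Hypothesis section concerns the whole COPE-ICD programme, including its effect on fear of exercise and on physical capability. The programme starts at randomisation. The earliest exercise test comes about three months later, after contacts that already address avoidance of activity. It is therefore a post-randomisation measurement that may carry part of the programme's effect.

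It is also the only earlier exercise value, so it is the natural candidate for a change score or an adjustment covariate. Either use would change what is estimated, from the effect of the whole programme to something closer to the added effect of months 3 to 6. The within-group paired tests for this outcome can only compare 3 with 6 months, and they are not randomised comparisons.

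Separately, a pre-randomisation measure of physical capacity exists. The schedule in Table 2 does not show it, and the stated primary test makes no use of it.

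**Working it through.** **1. The plan's own figure.** Inputs from Sample size: difference 15%, SD 0.3, alpha 5%, power 80%. Read 15% as 0.15 on the scale of the SD, and take the test as two-sided.

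- Standardised difference: 0.15 / 0.3 = 0.5.
- Normal approximation: n per arm = 2 × (1.96 + 0.842)² / 0.5² = 62.8, so 63 per arm and 126 in total.
- Exact two-sample t-test: 64 per arm, 128 in total. This is the stated number.

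The calculation has no change-score or correlation term. It fits a comparison of final values. It would fit a change score only if the correlation between the 3- and 6-month values were 0.5, because the SD of change is 0.3 × √(2(1 − ρ)), which equals 0.3 only at ρ = 0.5.

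**2. What each analysis estimates.** Let e6 be the between-arm effect at 6 months, e3 the effect already present at 3 months, and b the within-arm slope of the 6-month on the 3-month value (b = ρ if the SDs are equal).

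- 6-month value: e6, the effect of the programme up to 6 months.
- Change from 3 to 6 months: e6 − e3.
- 6-month value adjusted for the 3-month value: e6 − b × e3.
- Within-group paired change: no between-arm contrast, so time trend and treatment effect cannot be separated.

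**3. Illustration.** The article gives neither e3 nor ρ, so both are assumed. Take e6 = 0.15, SD 0.3 at each visit and 64 per arm.

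| e3 | Change estimates | Power, ρ = 0.5 | ρ = 0.7 | ρ = 0.8 |
|---|---|---|---|---|
| 0 | 0.15 | 80% | 95% | 99% |
| 0.03 | 0.12 | 61% | 83% | 94% |
| 0.05 | 0.10 | 47% | 68% | 84% |

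The 6-month comparison keeps 0.15 and 80% power in every row. If e3 is above zero, the change score gives a smaller estimate whatever ρ is. Its power can be lower or higher than 80%, because a high correlation shrinks the SD of change (0.232 at ρ = 0.7, 0.190 at ρ = 0.8). The firm consequence is a different estimand, not a loss of power.

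**4. Gain from a true baseline covariate.** Let r be the correlation between baseline 6MWT and the 6-month exercise result. The article does not give it; 0.5 to 0.6 is assumed. Residual variance is 1 − r² of the unadjusted variance.

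- r = 0.5: 1 − 0.25 = 0.75, a fall of 25%.
- r = 0.6: 1 − 0.36 = 0.64, a fall of 36%.

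The standard error is multiplied by √0.75 = 0.87 or √0.64 = 0.80. The covariate was measured before allocation, so the estimate still targets e6.

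**5. Schedule.** Table 2 lists 6MWT at 3 and 6 months only. Table 5 and the Baseline measures text report it at baseline by arm. The two do not agree.

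**The case against.** Much of the case on the other side stands.

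- **The primary may already be the right one.** A reader might infer that change from 3 months is the planned primary endpoint. No sentence says so. The primary comparison is between groups, the 128 reproduces as a plain two-group comparison, and the paired tests are confined to within-group analysis. A 6-month between-arm comparison is valid without any baseline.
- **A change score would still be a randomised contrast.** A reader might infer that between-arm change from 3 months is no randomised effect at all. With complete follow-up it is one, namely the 6-month effect minus the 3-month effect. It answers a narrower question than the hypothesis.
- **The pre-training label is accurate.** Training starts at 3 months, and the article does not call this test a baseline. The earlier exposure is psycho-education only, and Table 1 puts the explicit avoidance question at one consultation.
- **The baseline 6MWT is not shown to be discarded.** It is reported, and the regression models do not exclude it. A predefined statistical protocol is cited but not at hand; it may settle final value versus change and the covariates.
- **Drop-out.** Patients lost before 3 months are also missing at 6 months, so a 6-month comparison does not recover them. That is a separate matter.

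What remains is that the article names an unadjusted t-test as primary, leaves its outcome variable open where the only earlier value is post-randomisation, and prints a 6MWT schedule that disagrees with its own results table.

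**Conclusion.** The point holds as an improvement to make, not as proof that the planned analysis is invalid. The exercise co-primary has no pre-randomisation value. Using the 3-month test as baseline or covariate would remove all or part of any effect reached by then, and the within-group 3-to-6-month tests cannot show an effect of the programme. The size of any 3-month effect is unknown and may be zero.

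The quantified gain is in precision: 25% to 36% less residual variance than the stated t-test, resting on an assumed correlation of 0.5 to 0.6. A weaker correlation would give less. The omission in Table 2 is a plain inconsistency and needs no assumption.

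**What to change.** 1. State that the exercise primary is the 6-month value compared between arms by ANCOVA, adjusted for baseline 6MWT distance, gender and LVEF stratum.
2. State that the 3-month exercise test is an intermediate outcome and serves neither as baseline nor as covariate in that analysis. Label the paired within-group tests as descriptive.
3. In the 6MWT analysis, use the baseline 6MWT as the covariate.
4. Add Baseline to the 6MWT row of Table 2.

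The cost is wording and covariates already collected. No visit, test or patient is added. If the predefined statistical protocol already fixes items 1 to 3, only the article's wording and Table 2 need correcting.
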